### Outcome measures

The primary outcome is the severity of depressive symptoms during the year following the intervention relative to baseline. Depressive symptoms are repeatedly assessed with the IDS-SR. Mixed effects regression analysis will estimate the integrated treatment effect on all four follow-up IDS-SR assessments from T1 (7 weeks, directly after the six-week intervention) to T4 (52 weeks), relative to T0 (baseline).

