### Sample size calculation

Sample size calculations for mixed effect regression models require a number of estimates, or assumptions [61]. We estimate an average dropout of 3% with every next assessment (all-completers at T0, 3% drop-out at T1 to 12% drop-out at T4). We estimate the (within-subject) intraclass correlation coefficient (ICC) of the pre-assessment and four follow-up assessments to be approximately 0.50. A somewhat higher ICC will slightly inflate the minimal detectable effects, a somewhat lower ICC will slightly lower the minimal detectable effects. In the two by two factorial intervention design, the ratio of participants who will receive CBT-I versus those who will not is 1. This is also the case for those who will receive CT versus those who will not. For the interaction effect of CBT-I x CT, the ratio of participants who will receive both interventions versus those who will not is 1/3. We follow Cohen’s suggestion that an effect size below *d* = 0.2 (small) is not likely to be clinically significant, that *d* = 0.5 represents a medium effect size, and that *d* = 0.8 represents a large effect size [62]. A feasible total number of completers (i.e. complete data on the ambulatory recordings, EEG sleep recordings, MRI and questionnaires) at baseline is *N* = 120, *N* = 30 for each of the four groups, of whom we assume that *N* = 26 per group will complete all follow-up assessments. At a significance threshold of *α*  = 0.05, this sample size provides a power 1-*β*  = 0.80, the minimal detectable interaction effect is *d* = 0.5, while the minimal detectable main effects of either CBT-I or CT are *d* = 0.44 (medium). A previous similar study reported a more than medium effect of CBT-I on depressive symptoms at T1 (*d* = 0.74) up to a large effect at T4 (*d* = 1.12) [63].

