### Statistical analyses

Statistical analyses aim at determining the relative efficacy of internet-guided CBT-I, CT treatments and their combination, for the prevention of worsening of depressive symptoms in people with the type of ID that heralds increased risk of developing depression. The long-term effects of interventions and their interactions on depressive symptoms and on the probability to develop a diagnosis of depression will be estimated with mixed effect linear and logistic regression models using R [45].

In order to allow for an intention-to-treat analysis including all available data while accounting for a possibly variable number of missing data, hierarchical mixed effect linear and logistic regression models will be employed. Regressors are a random intercept, time, dummy-coded assignment to CBT (yes = 1, no = 0) and CT (yes = 1, no = 0) and a dummy coded variable indicating follow-up (T1-T4 = 1) versus baseline (T0 = 0). The interaction effect estimates of interest are CBT by follow-up, CT by follow-up and CBT-I by CT by follow-up [64]. The time variable estimates linear changes over time. Ancillary analyses will evaluate treatment by time effects (i.e., treatment effects changing linearly over time). Linear mixed effect models will also be used evaluate secondary outcomes (insomnia severity, cost-effectiveness, brain function and structure). A logistic mixed effect model will be used to evaluate the secondary outcome of a diagnosis of depression at T4. We will explore the effect of various variables, including the number of previous depressive episodes, time since last depressive episode, and expectation of intervention effectiveness.

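### The single T0 IDS-SR carries 80% of the variance of the primary contrast; adjusting for it cuts that variance by 40% without new data, and a second pre-treatment score would add a smaller gain

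*Protocol article*

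**What the plan says.** The protocol article, under Outcome measures, defines the primary effect as follows: "integrated treatment effect on all four follow-up IDS-SR assessments from T1 (7 weeks, directly after the six-week intervention) to T4 (52 weeks), relative to T0". Table 1 marks the IDS-SR once before treatment (T0) and at T1 to T4. The ISI is marked at enrolment and again at T0, and the ITQ at enrolment.

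Statistical analyses lists the model terms: "Regressors are a random intercept, time, dummy-coded assignment to CBT (yes = 1, no = 0) and CT (yes = 1, no = 0"), together with "a dummy coded variable indicating follow-up (T1-T4 = 1) versus baseline (T0 = 0"). The targets are these: "The interaction effect estimates of interest are CBT by follow-up, CT by follow-up and CBT-I by CT by follow-up". Because the treatment terms stand in the model beside the follow-up indicator, the groups may have different means at T0.

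Sample size calculation gives one correlation for all five assessments: "We estimate the (within-subject) intraclass correlation coefficient (ICC) of the pre-assessment and four follow-up assessments to be approximately 0.50". It takes 120 participants as the feasible number, assumes 26 completers per cell, and states a minimal detectable main effect of d = 0.44 at 80% power. Under Randomization, baseline IDS-SR is one of the matching variables.

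**The concern.** The follow-up side of the contrast averages four scores, while the baseline side is one score taken at face value. Measurement noise and day-to-day variation in that one questionnaire pass undiluted into every primary estimate. With the sample size fixed by feasibility, the handling of baseline is one of the few places where precision can still be gained. More follow-up would do little: a fifth follow-up lowers the variance only from 0.625 to 0.5 × (1 + 1/5) = 0.600. At stake are the width of the primary intervals and the smallest effect the trial can detect. The validity of the comparison is not in question.

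**Working it through.** **Inputs.** From the article: ICC 0.50, one T0 and four follow-up scores, random intercept only, 26 completers per cell (52 v 52 for a main effect), α = 0.05, power 0.80. Assumed: a two-sided test, and a correlation r between two pre-treatment scores, which the article does not give. Variances are in units of the IDS-SR variance.

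**1. The plan's own figure.** The random intercept cancels in the change contrast, leaving

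V = (1 − ICC)(1 + 1/4) = 0.5 × 1.25 = 0.625.

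Detectable d = 2.80 × √(V × 2/52) = 0.434, in line with the stated 0.44. Power at d = 0.44 is 81%. At ICC 0.50 the follow-up mean alone also has variance (1 + 3 × 0.5)/4 = 0.625, so the stated figure does not show which formula was used.

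**2. Share of the baseline.** T0 contributes 0.5 × 1 = 0.5 and the follow-ups 0.5/4 = 0.125. The T0 share is 0.5/0.625 = 80%, whatever the ICC. With the planned drop-out (about 3.7 follow-ups per person) it is about 79%.

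**3. Adjusting for the existing T0 score.**

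V = (1 + 3 × ICC)/4 − ICC² = 0.625 − 0.25 = 0.375, a 40% cut.

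Detectable d falls to 0.336 and power at d = 0.44 rises to 96%. The cut depends on the ICC: from 0.875 to 0.385 (56%) at ICC 0.3, and from 0.375 to 0.285 (24%) at ICC 0.7. A generalised least squares calculation for the factorial model with linear time, 30 per cell and 3 to 12% drop-out agrees. Constraining T0 means lowers detectable d from 0.411 to 0.322, a 39% cut in variance.

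**4. Adding a second pre-treatment score.** The mean of the two has variance (1 + r)/2. Used as the covariate, it gives V = 0.625 − 0.25 × 2/(1 + r). Used as the baseline of a change contrast, it gives V = 0.625 + (1 + r)/2 − 1.

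| r | Adjusted V | Cut from 0.375 | Detectable d | Change V | Cut from 0.625 | Detectable d |
|---|---|---|---|---|---|---|
| 0.5 | 0.292 | 22% | 0.297 | 0.375 | 40% | 0.336 |
| 0.8 | 0.347 | 7% | 0.324 | 0.525 | 16% | 0.398 |
| 0.9 | 0.362 | 3.5% | 0.330 | 0.575 | 8% | 0.417 |

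**5. What the planned model would report.** The right-hand columns are true variances. The random-intercept model with one residual variance does not reproduce them.

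- *Averaged T0 row.* The pooled within-person variance over five rows is [4 + (1 + r)/2 − (14 + (1 + r)/2)/5]/4 = 0.45, 0.48 or 0.49 at r = 0.5, 0.8 or 0.9. Multiplied by 1.25, the reported V is 0.5625, 0.600 or 0.6125, so the standard error is overstated. Power at d = 0.44 becomes 90%, 84% or 83%, against 96%, 87% or 84% with a correct standard error.
- *Two separate rows at r = 0.8.* The pooled within-person variance over six rows is [6 − (6 + 1.6 + 14)/6]/5 = 0.48. The reported V is 0.48 × (1/2 + 1/4) = 0.36, against a true 0.525. The critical value is in effect 1.96 × √(0.36/0.525) = 1.62, a type I error of about 10%.

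**The case against.** The strongest reply is that nothing here is stated wrongly. One baseline score is ordinary, and the stated d = 0.44 reproduces. The article also cites CBT-I effects of d = 0.74 to 1.12 from a similar study, and at 0.74 planned main-effect power already exceeds 99%. That stands, and it makes this a matter of precision only. The article gives no expected effect for CT, however, so the comfort does not extend to that arm.

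Second, allocation matches on baseline IDS-SR, so actual T0 imbalance will be smaller than the model assumes. This also stands. With exact balance, the true variance of the contrast would be 0.375 even in the planned model. That model would still report about 0.625, and its tests would use the larger value. Power at d = 0.44 would then be Φ[(0.44 − 1.96 × 0.155)/0.120] = 87%, against 96% with adjustment. Matching therefore supports adjusting for T0.

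A reader might infer from the 80% share that measuring once is the fault, and that a second questionnaire would by itself cut the variance by 40% and lift power to 96%. The documents do not support that. The share arises because T0 means are left free, and adjusting for the existing score gives the same 40%. The 40% from a second score needs two closely spaced scores to correlate no more than scores up to a year apart, and no such correlation is given. The planned model would also not report that gain correctly.

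**Conclusion.** The point holds as a worthwhile gain in precision on the primary outcome. Under the plan's own model and ICC, the single T0 IDS-SR supplies 0.5 of the 0.625 variance. Most of the recoverable loss is in the analysis: adjusting for T0, or constraining T0 means, lowers detectable d from 0.434 to 0.336 at ICC 0.50. A second pre-treatment score is a smaller addition, worth 22% of the adjusted variance at r = 0.5 but only 7% at 0.8 and 3.5% at 0.9. The lower end is the more plausible for scores taken close together.

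These figures assume two-sided tests, exchangeable correlations of 0.50 apart from r, and main effects at 52 v 52 as in the sample size section. It would go too far to conclude that the primary comparison is biased or that the stated power is wrong for the change contrast.

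**What to change.** 1. **Primary model.** Include T0 IDS-SR as a covariate for the T1 to T4 scores, or keep T0 as an outcome and constrain its mean to be equal across the four randomised groups. This needs no new data. Baseline assessments are completed before participants learn their allocation, so the constraint is justified.
2. **Cheap addition.** In Table 1, add the IDS-SR at enrolment beside the ISI and ITQ, or give it at the start and end of the 9-day T0 period. Use the mean of the two scores as the covariate. The cost is one short self-report form with no added visit, which people later found ineligible would also complete. Under Trial status, data collection has begun, so only later entrants would have two scores, and the analysis must say how one-score and two-score participants are combined.
3. **If the change-from-baseline model is kept.** Give the pre-treatment value or values their own variance and covariance with follow-up. Neither an averaged T0 row under one residual variance nor two rows under a random intercept alone is acceptable.
4. **Secondary ISI analysis.** The enrolment ISI already exists and could serve as a second pre-treatment value. It needs its own visit mean, because an ISI threshold is an eligibility criterion, and the covariance condition in item 3 applies.
5. **Sample size section.** Restate the minimal detectable effects for the model actually used, with the assumed correlation between the pre-treatment scores and a range around it.

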### Participants

The RCT aims to include 120 people with ID of the subtypes with increased risk of developing depression. Inclusion criteria are: 1) meeting the criteria of ID according to the Diagnostic and Statistical Manual of Mental Disorders, 5th edition (DMS-5) [35], and the International Classification of Sleep Disorders, 3rd edition (ICSD-3) [36]; 2) an Insomnia Severity Index score (ISI) ≥ 10 [37]; 3) classification as insomnia type 1, 2, or 3 according to the Insomnia Type Questionnaire [8]; and 4) age between 18 and 70 years. Exclusion criteria are: a) current major depressive disorder according to self-report, a clinical diagnosis, or the Composite International Diagnostic Interview Short Form (CIDI-SF) [38]; b) current treatment with antidepressant medication; c) current CBT-I treatment; d) a diagnosis of or probable severe obstructive sleep apnea syndrome (Apnea Hypopnea Index ≥15 [39], or high risk according to the Berlin questionnaire [40]), moderate to severe restless legs syndrome (International Restless Legs Scale > 15 [41]), or severe periodic limb movement disorder (Periodic Limb Movement Index ≥ 25); e) a self-reported diagnosis of a severe neurological or psychiatric disorder; f) self-reported severe physical or mental impairment due to stroke, or traumatic head injury; g) night work or rotating shift-work; h) a known eye condition incompatible with light exposure; i) a history of light-induced migraine or epilepsy, or severe side effects to bright light in the past; or j) MRI contraindications such as non-MR compatible metal implants, claustrophobia, or pregnancy. The use of sleep medication is allowed and monitored. Participants will be recruited among the participants of the Netherlands Sleep Registry (www.sleepregistry.org), through media advertisements, and through flyers. It will be documented whether participants were recruited from the sleep registry or via media advertisements and flyers.

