### Assessment points and measures

In participants of the RCT, repeated assessments take place at baseline (T0), during the 6-week treatment period (T_intervention_), and at four follow-up time points (T1, week 7; T2, week 26; T3, week 39; T4, week 52). Table 1 shows the assessments for each time point (according to the Standard Protocol Items: Recommendations for Interventional Trials (SPIRIT) guidelines; the full SPIRIT Checklist is available as Additional file 1). For all participants, the baseline assessments (T0) include an MRI scan, 9 days of actigraphy monitoring and sleep diaries (Consensus Sleep Diary, CSD [46]), and questionnaires assessing demographics, mood (IDS-SR [43]; Hospital Anxiety and Depression scale, HADS [47]; Positive Affect Negative Affect Scale, PANAS [48]), anxiety (Beck Anxiety Inventory, BAI [49]), sleep (ISI [37]; Pittsburgh Sleep Quality Index, PSQI [50]; Duke Structured Interview for Sleep Disorders for DSM-5, DSISD [51]; sleep history; Munich Chrono Type Questionnaire, MCTQ [52]; reduced Morningness-Eveningness Questionnaire, rMEQ [53]), life events (Life Experience Survey, LES-B [54]), childhood trauma (Childhood Trauma Questionnaire, CTQ [55]), physical exercise (Baecke questionnaire [56]), and cost-effectiveness (Trimbos and iMTA questionnaire on Costs associated with Psychiatric Illness, TIC-P [57]). A diagnostic interview (CIDI-SF [38]) is administered to assess a diagnosis of major depressive disorder according to the DSM-IV criteria [58].

**Table 1 Tab1:** Overview of interventions, assessments, and timepoints

		Study Period					
	Enrolment	Baseline	Intervention	Follow-up assessments			
**Timepoint**	**-t**_1_	**T**_0_	**T**_intervention_	**T**_1_	**T**_2_	**T**_3_	**T**_4_
		*Week 0*	*Week 1–6*	*Week 7*	*Week 26*	*Week 39*	*Week 52*

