**Assessments:**							
***Demographics***		X					
***CIDI-SF***^1^		X					X
***IDS-SR***^2^		X		X	X	X	X
***HADS***^3^		X		X	X	X	X
***PANAS***^4^		X		X	X	X	X
***Actigraphy***		X		X			X
***CSD***^5^		X	X	X			X
***ISI***^6^	X	X		X	X	X	X
***PSQI***^7^		X					
***DSISD***^8^		X					
***Sleep history***		X					
***MCTQ***^9^		X					
***rMEQ***^10^		X					
***ITQ***^11^	X				X		X
***BAI***^12^		X		X	X	X	X
***LES-B***^13^		X			X	X	X
***CTQ***^14^		X					
***TIC-P***^15^		X					X
***Baecke***		X					
***Compliance***			X				
***Use of interventions***					X	X	X
***Health care use***					X	X	X
***MRI***^16^		X		X			

^1^ Composite International Diagnostic Interview – Short Form, ^2^ Inventory of Depressive Symptoms – Self Report, ^3^ Hospital Anxiety and Depression Scale, ^4^ Positive Affect Negative Affect Scale, ^5^ Consensus Sleep Diary, ^6^ Insomnia Severity Index, ^7^ Pittsburgh Sleep Quality Index, ^8^ Duke Structured Interview for Sleep Disorders, ^9^ Munich Chronotype Questionnaire, ^10^ reduced Morningness-Eveningness Questionnaire, ^11^ Insomnia Type Questionnaire, ^12^ Becks Anxiety Inventory, ^13^ Life Experience Survey, ^14^ Childhood Trauma Questionnaire, ^15^ Trimbos and iMTA questionnaire on Costs associated with Psychiatric Illness, ^16^Magnetic Resonance Imaging

During treatment (T_intervention_), participants randomized to CBT-I (and in combination with CT) fill out the CSD every day during week 1–6 (T_intervention_). Participants randomized to CT (and in combination with CBT-I) fill out a questionnaire about the compliance to the chronobiological interventions every day during week 1–6 (T_intervention_).

The assessments at T1 (week 7) include an MRI scan, 7 days of actigraphy monitoring and sleep diaries (CSD), and questionnaires assessing mood (IDS-SR, HADS, PANAS), anxiety (BAI), and insomnia (ISI). At T2 (week 26) and T3 (week 39) participants fill out questionnaires assessing mood (IDS-SR, HADS, PANAS), anxiety (BAI), insomnia (ISI), insomnia types (ITQ), life events (LES-B), use of therapy interventions and use of health care. After 1 year (T4) participants wear an actigraph for 7 days, fill out sleep diaries for 7 days (CSD), are interviewed to assess a diagnosis of major depressive disorder (CIDI-SF), and fill out questionnaires assessing mood (IDS-SR, HADS, PANAS), anxiety (BAI), insomnia (ISI), insomnia types (ITQ), life-events (LES-B), cost-effectiveness (TIC-P), use of therapy interventions, and use of health care.

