### Secondary measures

A secondary outcome is a diagnosis of major depressive disorder based on the CIDI-SF at T4 (52 weeks) relative to T0 (baseline). Other secondary outcome measures are the severity of insomnia and the cost-effectiveness of each treatment calculated from health care and work absenteeism. Severity of insomnia will be measured with the ISI, CSD and actigraphy recordings. Cost-effectiveness will be assessed with the TIC-P questionnaire. Another secondary outcome measure is the effect of the intervention (CBT-I and/or CT) on brain structure and function (assessed with MRI) at T1 relative to T0.

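### The logistic mixed model named for MDD diagnosis is not identified: no T0 event is possible, and T4 alone gives one binary value per participant

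*Protocol article*

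**What the plan says.** All statements are in the protocol article.

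- **Outcome (Secondary measures).** "A secondary outcome is a diagnosis of major depressive disorder based on the CIDI-SF at T4 (52 weeks) relative to T0 (baseline").
- **Eligibility (Participants).** Among the exclusions is "current major depressive disorder according to self-report, a clinical diagnosis, or the Composite International Diagnostic Interview Short Form (CIDI-SF").
- **Timing (Assessment points and measures, Table 1).** At baseline, "A diagnostic interview (CIDI-SF [38]) is administered to assess a diagnosis of major depressive disorder according to the DSM-IV criteria". At one year, participants "are interviewed to assess a diagnosis of major depressive disorder (CIDI-SF"). The CIDI-SF row of Table 1 is marked at T0 and T4 and nowhere else.
- **Model (Statistical analyses).** One hierarchical specification serves both the linear and the logistic models: "Regressors are a random intercept, time, dummy-coded assignment to CBT (yes = 1, no = 0) and CT (yes = 1, no = 0"), plus a dummy for follow-up against baseline. "The interaction effect estimates of interest are CBT by follow-up, CT by follow-up and CBT-I by CT by follow-up". For MDD the section then says: "A logistic mixed effect model will be used to evaluate the secondary outcome of a diagnosis of depression at T4".

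No other repeated binary measure of MDD is described, and no separate single-time-point model is given for it.

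**The concern.** The specification suits the IDS-SR, which is measured five times and varies at baseline. It does not carry over to a diagnosis that is measured twice and is absent in everyone on the first occasion. The model can be read as using T0 and T4, or T4 only. On each reading some of its terms cannot be estimated.

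At stake is the one outcome that directly addresses the onset of a diagnosed depression, obtained by interviewers blinded to condition. If the named model does not give usable estimates, the analyst has to choose a replacement once the data are in hand. The choice matters more than usual because few events are expected.

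**Working it through.** **Inputs.** From Sample size calculation: 30 randomised per arm, 12% dropout at T4, 26 completers per arm. From Background: 13% of people with insomnia develop depression within a year. Assumed here: base rates of 20% and 25%, because the article gives no rate for the three selected subtypes; and, for illustration only, 5, 3, 3 and 2 events of 26 under TAU, CBT-I, CT and the combination (13 in total).

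**1. The plan's own figure.** 30 x (1 - 0.12) = 26.4, so 26 per arm and 104 in total. This reproduces. The article states no event count or power for MDD.

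**2. Reading A: T0 and T4 rows.** All four T0 cells have zero events, so the likelihood rises as the T0 logit falls. With random-intercept SD 0, the log-likelihood on the illustrative data is:

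| T0 logit | log-likelihood |
|---|---|
| -2 | -51.576 |
| -4 | -40.263 |
| -10 | -38.381 |
| -20 and below | -38.376 |

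The same limit is reached with SD 1 and SD 2. No finite maximum exists. In an iterative fit of the fixed-effects part (no random intercept, time omitted):

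| Iterations | Follow-up coefficient (SE) | SE of CBT by follow-up |
|---|---|---|
| 10 | 10.1 (39) | 55 |
| 15 | 15.1 (471) | 666 |
| 20 | 20.1 (5,733) | 8,108 |
| 25 | 25.1 (69,842) | 98,771 |

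CBT-by-follow-up values of 9.4, -0.6 and -10.6 all give a log-likelihood of -38.375885. These interactions are the estimates that the plan declares to be of interest.

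With two visits, time (0, 52) is also 52 times the follow-up dummy (0, 1). The design has 9 columns and rank 8.

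**3. Reading B: T4 rows only.** There is one binary value per participant. With the random-intercept SD fixed at several values:

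| SD | maximised log-likelihood | CBT log-odds ratio (without CT) | SE | Wald z |
|---|---|---|---|---|
| 0 | -38.375885 | -0.60 | 0.79 | -0.762 |
| 1 | -38.375885 | -0.68 | 0.89 | -0.764 |
| 2 | -38.375885 | -0.89 | 1.16 | -0.766 |
| 5 | -38.375885 | -1.75 | 2.28 | -0.768 |

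The data cannot choose among these SDs. The size of the odds ratio depends on the choice; the fitted arm risks (5/26, 3/26, 3/26, 2/26) do not, and the test barely does. Ordinary logistic regression, the SD 0 row, gives CBT -0.60 (SE 0.79), CT -0.60 (SE 0.79) and interaction 0.15 (SE 1.24).

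**4. Expected events.** With base rate p and each treatment multiplying risk by h, the arm risks are p, ph, ph and ph². Expected total = 26 x p(1 + h)². The chance that at least one arm is empty = 1 - Π[1 - (1 - r)^26] over the four arm risks r.

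| p | Events, no effect | Events, each halves risk | Any empty arm, no effect | Any empty arm, halving |
|---|---|---|---|---|
| 13% | 104 x 0.13 = 13.5 | 26 x 0.13 x 2.25 = 7.6 | 10% | 62% |
| 20% (assumed) | 20.8 | 11.7 | 1.2% | 36% |
| 25% (assumed) | 26.0 | 14.6 | 0.2% | 24% |

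For 13% with halving: 0.87^26 = 0.027, 0.935^26 = 0.174 (two arms), 0.9675^26 = 0.424; 1 - 0.973 x 0.826² x 0.576 = 0.62.

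**The case against.** The strongest reply is that the sentence about MDD names the diagnosis at T4. Read that way, little is lost: the random intercept is superfluous, the arm risks are unchanged, and Wald z stays between -0.762 and -0.768 whatever SD is imposed. **This stands.** A reader might infer that MDD cannot be analysed at all, or that the software must fail. Neither is supported. The T4 comparison has a finite ordinary logistic solution on the illustrative data, and a program may still print numbers for the mixed model, such as a variance at zero or very large standard errors.

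It does not clear the text, however. The same section makes treatment-by-follow-up terms the effects of interest, and Secondary measures defines the outcome relative to T0, so the reading with T0 rows is a natural one. The T4 reading still leaves an odds ratio of undefined scale.

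A second reply is that the detail belongs to a statistical analysis plan. The article does not leave the model open, though: it names one and lists its regressors.

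Third, the event counts rest on a rate for insomnia in general, while the trial selects higher-risk subtypes. This also stands, hence the range. In addition, 13% is onset within a year, and the article does not state the recall window of the T4 interview, so the count could be lower or higher. Event counts do not bear on identifiability; they bear on which estimator to use.

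Finally, a reader might infer that so few events rule out the CBT-I x CT term. The section sets out to estimate interactions on the probability of a diagnosis, and the term is estimable, though imprecise.

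**Conclusion.** The specification is wrong as written for this outcome. With T0 rows, follow-up and its treatment interactions have no finite maximum-likelihood estimates and time is aliased with follow-up. With T4 alone, the random-intercept variance and the scale of the subject-specific odds ratio are not identified. These conclusions need only the exclusion of current MDD and the two-visit CIDI-SF schedule; they do not depend on any event rate.

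The reach is limited to one secondary outcome. The primary IDS-SR model and its sample size are unaffected. The likely sparsity of events is a separate and less certain matter: the chance of an empty arm, if each treatment halves risk, is 62% at 13% and 24 to 36% at assumed rates of 20 to 25%, given 26 completers per arm and multiplicative effects.

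**What to change.** Replace the MDD sentence with a single-level logistic regression of the T4 diagnosis on CBT, CT and CBT x CT. Omit the T0 rows, random intercept, time and follow-up terms; only this part follows strictly from the defect. Because an arm may have no event, specify Firth penalisation so that estimates stay finite, and report risk differences with confidence intervals.

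The cost is a few sentences of analysis wording, with no change to data collection. There are two downsides. The interaction will be very imprecise (SE 1.24 on the log-odds scale in the illustration). The model also uses only participants with a T4 interview, with about 12% expected to be missing, which sits uneasily with the stated intention-to-treat aim of using all available data. A missing-data sensitivity analysis, for example multiple imputation that draws on the repeated IDS-SR scores, should accompany it.
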